#### Statistical Analysis of Secondary Outcome #2

The exact values of white matter structure expressed as the diffusion coefficient (Fractional Anisotropy value) of the relevant pain related areas will be extracted, and separate statistical analyses will be performed. To test the association between the white matter microstructure extracted following analysis using TBSS/DTI and the area of secondary hyperalgesia, individual measures computed from the TBSS and DTI will be investigated by linear regression.

#### Statistical Analysis of Exploratory Associations #1-4

From the T1-weighted 3D anatomical scans, volume estimates of the caudate nuclei (mm^3^) will be exported to a spreadsheet for regression analysis to assess the association between volume of caudate nucleus and the score of HPDT, p-TS-max, p-TS VAS-AUC, PCS, and HADS respectively. The association of the volume of the right and left caudate nucleus and HPDT, p-TS-max, p-TS VAS-AUC, PCS and HADS will be investigated by linear regression of the EBLUPS in relation to the volume of caudate nucleus.

Significance of the ability of the caudate nucleus’ volume as a predictor will be assessed by ANOVA methods. The ability of the caudate nucleus’ volume to predict individual variations in HPDT, p-TS-max, p-TS VAS-AUC, PCS, and HADS will be investigated by linear regression on the EBLUPS of the individual volumes of the caudate nucleus. Significance of the caudate nucleus as a predictor will be assessed by ANOVA methods and in case of significance, the predictive ability will be quantified by summary of prediction error, including 95% prediction interval. Relevant examples will be presented illustrating how accurately the volume of the caudate nucleus predicts HPDT, p-TS-max, p-TS VAS-AUC, PCS, and HADS in individual participants, or vice versa.

#### Statistical Analysis of Exploratory Associations #5-6:

Quantile-quantile plots and Shapiro Wilk’s test will be applied in assessment of normal distribution. If data are not normally distributed, Mann-Whitney U-test will be applied. If data are normally distributed, unpaired t-tests will be applied to investigate structural differences in brain volume, differences in white matter, and differences in rs-fMRI between the groups. To investigate potential differences in rs-fMRI, correction for multiple comparisons will be conducted by the MRI software using False-Discovery-Rate. Values of secondary hyperalgesia areas will be entered into the FSL-software, and a t-test will be performed.

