### Study Participants

Healthy male volunteers will be included in the study. The study participants will receive information regarding possible risks and side effects, and will be provided with written and oral information concerning the study. The participants will receive €67 (US $74) for their participation in the study. Inclusion and exclusion criteria are presented in Table 1.

**Table table1:** Inclusion, and exclusion criteria.

Inclusion criteria	Exclusion criteria
Age ≥18 years and ≤35 years	Study participants who cannot cooperate to the test
Male sex	Study participants with a substance abuse, assessed by the investigator
Study participants who have a weekly intake of >21 units of alcohol, or a have consumed >3 units of alcohol within 24 hours before experimental day Speak and understand the Danish language Signed informed consent Have participated and completed the study: “*To determine the degree of association between Heat Pain Detection Threshold and area of secondary hyperalgesia following Brief Thermal Sensitization in healthy male volunteers”* (Clinicaltrials.gov Identifier: NCT02527395)	Study participants who have consumed analgesics within 3 days before experimental day Study participants who have consumed antihistamines within 48 hours before experimental day Study participants who have consumed antidepressant medication within 30 days before the study Study participants who have consumed prescription medicine within 30 days before the study Study participants with neurological illnesses Study participants with chronic pain
	Study participants with psychiatric diagnoses
	Study participants with eczema, wounds, or sunburns on the sites of stimulation
	Study participants with a Body Mass Index of >30 kg/m^2^ or <18 kg/m^2^
	Study participants with contraindications to MRI^a^
	Study participants that decline information regarding potential pathological findings in relation to the MRI
	Study participants that have any kind of trauma resulting in pain and administration of analgesics in the period between experimental pain testing and MRI scan
	Study participants that experience a head trauma in the period between the experimental pain testing and the MRI scan
	

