#### Exploratory Outcomes

We will investigate the association between the volume of the left and right caudate nuclei and the following six parameters: (1) HPDT score, (2) p-TS max, (3) p-TS visual analog scale-area under the curve (VAS-AUC), and (4) the score of PCS-total, PCS-subscores, HADS-total, and HADS-subscores. When comparing healthy volunteers with a large (upper quartile) versus small (lower quartile) area of secondary hyperalgesia following BTS, we plan to investigate (5a) structural differences (volume) and the association with the size of the area of secondary hyperalgesia, (5b) differences in the association between area of secondary hyperalgesia and regions of interest extracted from TBSS, and (5c) differences in white matter microstructure in connections between pre specified pain related areas by white-matter tractography. In addition, we will examine (6) differences in resting state networks measured by rs-fMRI using independent component analysis (ICA; dual regression method).

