### Sample Size Estimation

Based on results from a previous study [11], sample size calculations are based on a Z-test of the Fisher transformed Pearson correlation. With a true correlation of r=-0.4 between the area of secondary hyperalgesia and the caudate nuclei, and a significance level of 2.5% to 5% according to the single step method (refer to *Statistical Significance*), a sample size of 52 is needed to obtain a power of 0.80 (β=0.20).

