### Statistical Analyses

#### Statistical Analysis of Primary Outcome

The estimates of the volumes, from the T1-weighted 3D anatomical scans of the caudate nuclei (mm^3^), will be exported to a spreadsheet for regression analysis to assess the association between volume of caudate nuclei and secondary hyperalgesia areas. The association of the volume of the left and right caudate nuclei and the area of secondary hyperalgesia will be investigated by linear regression of the estimated best linear unbiased predictors (EBLUPS) on the individual volumes of the left and right caudate nuclei. The ability of the volume of caudate nuclei to predict individual variation in the area of secondary hyperalgesia will be investigated by linear regression on the EBLUPS as a function of the individual volumes of the caudate nuclei.

Significance of the caudate nuclei as a predictor will be assessed by analysis of variance (ANOVA) methods and the predictive ability will be quantified by summary of prediction error, including 95% prediction interval for the prediction of the size of the area of secondary hyperalgesia. Relevant examples will be presented illustrating how accurately the volume of the caudate nuclei predicts the area of secondary hyperalgesia in the individual participants or vice versa. The association will be expressed in R^2^and prediction intervals for the area of secondary hyperalgesia given fixed values of the caudate nucleus’ volume. All analyses of structural MRI data (both in the primary, secondary, and exploratory outcomes) will be adjusted for age.

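### The quartile comparison of brain volumes (exploratory outcome 5a) is given only covariate-free tests, although the protocol promises age adjustment for every structural MRI analysis

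*Protocol article*

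**What the plan says.** Four places in the protocol article bear on this.

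- **Statistical Analysis of Primary Outcome** ends with a general rule: "All analyses of structural MRI data (both in the primary, secondary, and exploratory outcomes) will be adjusted for age". It sits in the primary-outcome section, but its wording reaches the exploratory outcomes.
- **Exploratory Outcomes**, item 5, compares "healthy volunteers with a large (upper quartile) versus small (lower quartile) area of secondary hyperalgesia following BTS". Item 5a concerns "structural differences (volume) and the association with the size of the area of secondary hyperalgesia". Items 5b and 5c concern diffusion measures: TBSS regions of interest and tractography.
- **Statistical Analysis of Exploratory Associations #5-6** sets the tests. "Quantile-quantile plots and Shapiro Wilk’s test will be applied in assessment of normal distribution". After that, "If data are not normally distributed, Mann-Whitney U-test will be applied", and "If data are normally distributed, unpaired t-tests will be applied to investigate structural differences in brain volume". No covariate, regression model or prior removal of age is mentioned.
- **Data Analysis Plan, T1-Weighted 3D Anatomical Images** adjusts all volumes for total intracranial volume, to remove the effect of head size. Age is not part of that step.

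**The concern.** Outcome 5a is plainly a structural MRI analysis, so the age rule applies to it. The tests named for it take two samples and nothing else. An analyst who follows the section on outcomes 5 and 6 to the letter produces an unadjusted comparison and breaks the general rule. An analyst who follows the general rule must invent a route that the protocol does not describe.

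The other volume analyses (primary, secondary #1, exploratory 1 to 4) do not have this problem. They are linear regressions, and age enters as one more term.

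Two things are at stake. First, the 5a result would be set beside age-adjusted results on the same volumes, and a difference between them could come from the handling of age rather than from anatomy. Second, under Ethics the protocol assigns outcomes 5 and 6 to a separate second publication, so 5a would be a leading result of that paper.

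**Working it through.** **1. The rules side by side.**

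| Element | Age rule (primary-outcome section) | Rule for 5a (section on outcomes 5-6) |
|---|---|---|
| Scope | All structural MRI analyses, exploratory included | Volume differences between quartile groups |
| Covariate | Age | None |
| Method | Not fixed | Unpaired t-test or Mann-Whitney |
| Prior adjustment of volumes | – | Intracranial volume only |

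The protocol gives no step that brings age into 5a.

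**2. The plan's own figure.** The only stated size is N = 52, for the primary correlation ("With a true correlation of r=-0.4 between the area of secondary hyperalgesia and the caudate nuclei"). With the Fisher transformation, n = ((z for two-sided alpha + z for 0.80 power) / atanh(0.4))² + 3, where atanh(0.4) = 0.4236.

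- Alpha 0.05: ((1.960 + 0.842)/0.4236)² + 3 = 46.7, so 47.
- Alpha 0.025: ((2.241 + 0.842)/0.4236)² + 3 = 56.0, so 56.
- Single-step alpha of 0.0350, which corresponds to a correlation of 0.9 between the two test statistics: 52.

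So 52 lies inside the stated range of significance levels. Nothing below changes it.

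**3. Group size in 5a.** 52/4 = 13 per quartile, so 13 against 13 if all 52 are analysed.

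**4. Chance imbalance in age.** The eligibility range is "Age ≥18 years and ≤35 years". Assume ages are uniform over it.

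- SD = 17/√12 = 4.91 years.
- SE of the difference in mean age = 4.91 × √(2/13) = 1.92 years.
- Probability of a gap above 2 years in either direction: about 0.30.

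Effect of a 2-year gap on mean volume, for an assumed age-volume correlation r: |r| × 2/4.91. This is 0.08 SD for r = -0.2 and 0.16 SD for r = -0.4. The SE of the volume difference is √(2/13) = 0.39 SD. A typical gap therefore moves the estimate by well under one standard error.

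**5. When the unadjusted test is biased.** Simulated type I error with no true volume-area association, 13 against 13 drawn from 52. All correlations are assumptions.

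| Age-volume r | Age-area r | Unadjusted t-test | Group plus age |
|---|---|---|---|
| -0.2 | 0 | 4.9% | – |
| -0.4 | 0 | 5.0% | – |
| -0.2 | 0.2 | 5.4% | 4.6% |
| -0.3 | 0.3 | 7.9% | 4.5% |
| -0.4 | 0.3 | 11% | 5% |

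If age is unrelated to area, the unadjusted test keeps its level. Inflation needs age to be related to both.

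**The case against.** **The rules can be reconciled.** Volumes are already adjusted for intracranial volume before testing. Age could be removed in the same way and a t-test or Mann-Whitney test run on the result. The age rule is stated once for the whole plan, and the sections on secondary outcome #1 and exploratory outcomes 1 to 4 do not repeat it either. This stands as far as it goes: a reader might infer that the two rules are logically incompatible, and they are not. But the protocol describes no such step for age, and the pre-adjustment that it does describe names intracranial volume alone. Followed as written, 5a is unadjusted.

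**Scope.** A reader might extend the conflict to the whole of outcome 5. Only 5a is certainly structural volume. Whether 5b and 5c fall under the age rule depends on whether structural MRI includes diffusion imaging, which the protocol does not say.

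**Chance age gaps.** A reader might take the 30% chance of a gap above 2 years as evidence of bias. It is not: chance imbalance is ordinary sampling variation, already covered by the standard error.

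**The normality check.** Choosing between means and ranks by Shapiro-Wilk at n = 13 is tempting to call an error, because the test has little power there: about 18% for a gamma with skewness 1 and about 33% for a lognormal with sigma 0.5. The documents do not support that charge. The check also uses quantile-quantile plots, the distributions are assumed, and no harm to error control appears. With a switch to Mann-Whitney whenever either group fails Shapiro-Wilk, overall type I error was 5.2% to 5.4% across normal, gamma, lognormal and exponential data in 10,000 runs each (Monte Carlo error about 0.2 points). Preferring a single pre-specified model is reasonable, but it is a preference.

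**Importance.** The Discussion says the sample was kept narrow in age and sex to limit such influences, and the outcome is exploratory. Both points stand and limit the weight of the concern.

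**Conclusion.** The inconsistency is real and confined to outcome 5a. The protocol promises age adjustment there and then specifies tests that do not provide it. It is not a detail deferred to another document, since both statements are in the current text.

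Its likely effect is modest. Unadjusted type I error stays near 5% if age is unrelated to area, is about 5.4% with correlations of 0.2 in size, and reaches about 8% to 11% only under the stronger assumed correlations of 0.3 to 0.4. These figures assume 13 per group, normal data and correlations that the protocol does not supply. The primary and secondary analyses and N = 52 are untouched.

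**What to change.** In the section on exploratory associations 5 and 6, replace the t-test/Mann-Whitney choice for 5a with one linear model per structure: volume, already adjusted for intracranial volume, on quartile group plus age. Check the residuals and, if wanted, give a permutation P-value as a sensitivity analysis.

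State whether structural MRI data in the age rule includes the diffusion measures of 5b and 5c. If it does, add age there in a model suited to each. The 5a model does not carry over unchanged, because 5b asks about differences in an association and neither 5b nor 5c analyses volumes.

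If the sponsor prefers to keep the two-sample tests, the alternative is to narrow the age rule so that it no longer covers 5a.

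The cost is a change of wording and one degree of freedom (26 - 3 = 23 residual degrees of freedom instead of 26 - 2 = 24). Age is already needed for eligibility and for the other adjusted analyses, so no new data are required.

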### Missing Data

For all analyses, an intention-to-test analysis will be performed including all subjects that participated in the experimental day. Analyses will be based on all observed data. In case of missing data exceeding 5%, and indication of violation of *missing completely at random* by a statistically significant Littles test, a sensitivity analysis based on an appropriate model for *missing data at random* or *missing data not at random* will be performed.

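### The only missing-data sensitivity analysis depends on a significant Little's test, which cannot rule out not-at-random missingness and has limited power at about 52 participants

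*Protocol article*

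**What the plan says.** The Missing Data section of the protocol article fixes three things.

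- **Analysis set:** an intention-to-test set, "including all subjects that participated in the experimental day".
- **Main handling:** "Analyses will be based on all observed data". For a linear regression of area on caudate volume, this means a complete-case analysis.
- **Sensitivity analysis:** one only, with two conditions joined by 'and'. It begins "In case of missing data exceeding 5%, and indication of violation of" missing completely at random, and that violation must be shown "by a statistically significant Littles test, a sensitivity analysis based on an appropriate model" for data missing at random or not at random.

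The section names no other missing-data check. It gives no expected missing rate, no significance level for Little's test and no list of variables to enter into it.

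**The concern.** This is a stated decision rule, not a detail left to a later document. Because both conditions must hold, a non-significant test means the planned check is not triggered, however much is missing.

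Two things are wrong with using Little's test in this way.

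1. **It cannot answer the question.** The test asks whether observed values differ between participants with different missingness patterns. It has no direct view of dependence on the missing value itself. Yet it decides whether a not-at-random model is fitted.
2. **Non-significance carries little information here.** At this sample size the 5% threshold is crossed at three people, so the test sets a handful of participants against the rest.

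The study calls itself confirmatory. At stake is whether the primary association between caudate volume and area could be distorted by selective loss of scans with no planned look at the question.

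**Working it through.** **Sample size, reproduced first.** Sample Size Estimation says "sample size calculations are based on a Z-test of the Fisher transformed Pearson correlation". Its inputs are r = −0.4, a level somewhere between 0.025 and 0.05 set by the single-step adjustment, power 0.80 and N = 52. Sidedness is not stated; two-sided is assumed.

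N = ((z(1−α/2) + z(0.80)) / atanh(0.4))² + 3, with z(0.80) = 0.842 and atanh(0.4) = 0.4236.

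- α = 0.05: ((1.960 + 0.842)/0.4236)² + 3 = 46.7, so 47.
- α = 0.025: ((2.241 + 0.842)/0.4236)² + 3 = 56.0, so 56.
- α = 0.035 (single-step level if the two test statistics correlate 0.9): ((2.108 + 0.842)/0.4236)² + 3 = 51.5, so 52.

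The stated 52 is reproduced and is used as n below.

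**When the first condition is met.** 2/52 = 3.8% and 3/52 = 5.8%, so at least three missing.

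**Power against a shift in an observed variable.** Assumptions: one missingness pattern with m people, q fully observed uncorrelated variables in the test, a mean shift of d SD in one of them, and a 5% test level. The statistic is approximately noncentral chi-square on q degrees of freedom with noncentrality λ = d²·m(n−m)/n. For m = 4 and d = 1, λ = 4 × 48/52 = 3.69.

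| d | m | λ | q = 1 | q = 3 | q = 6 |
|---|---|---|---|---|---|
| 1 | 3 | 2.83 | 0.39 | 0.26 | 0.20 |
| 1 | 4 | 3.69 | 0.48 | 0.33 | 0.25 |
| 1 | 5 | 4.52 | 0.57 | 0.40 | 0.30 |
| 0.5 | 3 | 0.71 | 0.13 | 0.10 | 0.08 |
| 0.5 | 4 | 0.92 | 0.16 | 0.11 | 0.09 |
| 0.5 | 5 | 1.13 | 0.19 | 0.13 | 0.10 |

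Direct simulation at m = 4 gives slightly lower values: 0.47, 0.31 and 0.20 for d = 1, and 0.16, 0.10 and 0.07 for d = 0.5.

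**Power and bias under missingness mechanisms.** Simulation with n = 52 and 4,000 replicates. Variables: area, age, left and right caudate volume, with both volumes missing together. The area-volume correlation is −0.4 (stated). Assumed: left-right correlation 0.9, test level 5%, chi-square on 2 degrees of freedom. Each entry is the proportion of trials with a significant test for 3 / 5 / 8 / 10 missing. The true standardised slope is −0.40.

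| Missingness depends on | Odds ratio per SD (per unit for the product) | Test significant | Complete-case slope |
|---|---|---|---|
| Nothing (completely at random) | – | 4 / 5 / 5 / 5% | −0.40 |
| Unseen caudate volume | 2 | 7 / 8 / 9 / 9% | near −0.40 |
| Unseen caudate volume | 3 | 8 / 11 / 14 / 16% | near −0.40 |
| Unseen caudate volume | 5 | 11 / 15 / 20 / 23% | near −0.40 |
| Product of volume and area | 3 | 19 / 16 / 13 / 11% | −0.32 / −0.27 / −0.21 / −0.18 |
| Observed area | 2 | 16 / 23 / 36 / 41% | −0.39 to −0.37 |
| Observed area | 3 | 32 / 51 / 69 / 80% | −0.38 to −0.34 |
| Observed area | 5 | 56 / 78 / 93 / 97% | −0.37 to −0.32 |

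For 3 to 5 missing, the not-at-random rows run from 7% to 19%; the 23% needs 10 missing. A repeat of the not-at-random simulations gave about 6% to 13% for the volume mechanism, and 11% to 20% for the product mechanism with slopes of −0.34 to −0.22.

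**Is this only a sample-size problem?** No. With n = 500, 50 missing and an odds ratio of 3, the test is significant in 100% of trials for the area mechanism and 74% for the volume mechanism, but only 14% for the product mechanism, where the slope is −0.26.

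**The case against.** A reader might infer something stronger: that Little's test can rarely be significant at this size, and that the observed-data result would then be taken as unbiased. The document does not support either.

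- **'Rarely' is too broad.** When missingness depends strongly on observed area (odds ratio 3 to 5) and five or more are missing, the test is significant in 51% to 97% of trials. In those rows, where area-driven bias is largest (slope −0.32), the test nearly always fires.
- **Nothing in the section says the result is treated as unbiased.** It says when a sensitivity analysis will be done and does not forbid one otherwise.
- **Informative missingness need not bias this slope.** Area is the outcome and volume the predictor. Area comes from a parallel study whose completion is an inclusion criterion, so gaps would fall mainly on volumes. If loss depends on volume alone, the complete-case slope stays near −0.40.
- **The damaging mechanism is somewhat contrived.** It needs joint dependence on volume and area, and area is blinded until the T1 image analysis is complete. With the product acting in the opposite direction, complete-case slopes were −0.42 to −0.47 and imputed slopes −0.42 to −0.46, so at-random imputation alone barely helps there.
- **Exposure is small.** There is one visit of about 50 minutes, no follow-up, and only attenders are analysed.

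All of this stands, and it limits the size and priority of the point. It does not justify the Little's-test condition itself: the test still cannot establish what the rule asks of it. Some loss is also possible, for instance through unusable scans.

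**Conclusion.** The point holds in a limited form. Making the only missing-data sensitivity analysis conditional on a significant Little's test is a poor rule, because the test cannot exclude not-at-random missingness at any sample size and has limited power with 3 to 5 of 52 missing. A non-significant result would often cancel the check without missing completely at random having been shown.

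The documents do not show that the primary result would be biased. Bias is little or none if loss depends on caudate volume alone, modest if it depends on area, and material if it depends on both jointly. Every power and bias figure rests on assumed missing counts, mechanisms, test variables and a 5% test level, since the protocol states none of these. Minor priority: missingness is likely to be low in this design.

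**What to change.** In Missing Data, remove the Little's-test condition and keep the 5% threshold, defined per analysis. Suggested wording: if more than 5% of the values in an analysis are missing, a sensitivity analysis will be performed by multiple imputation under missing at random, using variables already collected (age, HPDT, p-TS, PCS, HADS and available volumes), together with a not-at-random scenario over a pre-stated range of shifts in the imputed values; Little's test will be reported descriptively only.

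The range of shifts should be set before area is unblinded. It is worth letting the shift differ between participants with large and small areas, because the mechanism that harms the slope acts on volume and area together and a constant shift would not represent it.

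The cost is one sentence and a short script, with no extra work if 5% or less is missing. The sample size of 52 and the primary analysis are unchanged.
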